### Participants

2.2

#### Inclusion criteria

2.2.1

The patients were diagnosed with ischemic or hemorrhagic stroke with the lesion located in the left hemisphere, with a disease duration ranging from 1 to 12 months;The patients will undergo assessment for aphasia using the Western Aphasia Battery Revised (WAB-R), and the WAB-R aphasia quotient will be less than 93.8 points;Patients aged 18–75 years;Right hand;Normal language function before the onset of the disease;The native language is Chinese, primary school education or above (with more than 6 years of education).

#### Exclusion criteria

2.2.2

Aphasia caused by brain tumor, traumatic brain injury or other diseases;Contraindications to TMS treatment such as pacemakers, cochlear implants, or other metallic foreign bodies and any electronic devices implanted in the body;Combined history of epilepsy;Patients with severe cardiac, pulmonary, hepatic, renal, and other systemic diseases that cannot be controlled by conventional medication, as detected by laboratory examinations;Presence of a history of comorbid alcohol, drug, and other abuse;Patients who do not meet the inclusion criteria due to the presence of other examination abnormalities;Women of childbearing age who are pregnant or planning to become pregnant;Patients who have previously undergone TMS or transcranial electrical stimulation (TES) within 3 months before enrollment;Patients who are participating in other clinical research trials.

#### Withdrawal criteria

2.2.3

Severe adverse reactions or complications, such as persistent headaches, seizures, or other discomfort related to TMS;Protocol violations: Patients unable to comply with the study protocol, such as refuse to undergo assessments or interruption of treatment for more than 3 consecutive days;Development of new health issues or worsening of existing conditions deemed inappropriate for continued participation in the trial;Use of other TMS or TES treatments;Withdrawal from the trial without any specific reason.

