### Study design

2.1

This is a randomized, double-blinded, sham-controlled trial. The study will adhere to the ethical principles outlined in the Declaration of Helsinki and will follow the Consolidated Standards of Reporting Trials (CONSORT) guidelines (38), as well as the Recommendations for Interventional Trials (SPIRIT) (39). All patients who meet the inclusion and exclusion criteria will be randomly assigned in a 1:1 ratio to the following piTBS group and sham group after obtaining written informed consent. All patients will undergo corresponding assessments before treatment (T0), after treatment (T1), as well as during the 4-weeks follow up (T2). Please refer to Figure 1 and Table 1 for the specific study process. This study has been approved by the Medical Ethics Committee of the China Rehabilitation Research Center (No.2023-027-2) and registered in the Chinese Clinical Trial Registry (No. ChiCTR2300074533).

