#### Sample size

2.2.4

Based on the preliminary experimental results, the effect size [f(V)] for the piTBS group compared to the sham group in the primary outcomes is 0.25. With a significance level (α) of 0.05 and a power (1-β) of 0.95, considering a two-group design involving before and after treatment, and during follow-up assessments conducted at three time points, the anticipated sample size calculated using G*Power 3.1.9.7 for the repeated measures ANOVA model was 28. Anticipating a dropout/exclusion rate of around 10%, a total of 30 patients will need to be enrolled, with 15 patients allocated to each group.

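### The withdrawal criteria end trial participation, not only stimulation, so patients who stop before T1 can be lost from the primary WAB-R comparison

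*Protocol article*

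**What the plan says.** Section 2.2.3 (Withdrawal criteria) of the protocol article lists five grounds:

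- reactions to stimulation: "Severe adverse reactions or complications, such as persistent headaches, seizures, or other discomfort related to TMS";
- protocol violations, for which the examples are "refuse to undergo assessments or interruption of treatment for more than 3 consecutive days";
- new health problems, or "worsening of existing conditions deemed inappropriate for continued participation in the trial";
- use of other TMS or TES;
- leaving without giving a reason.

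The third and fifth grounds speak expressly of the trial, not of the study treatment. The section does not say that a patient who stops stimulation is still followed.

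Section 2.2.4 (Sample size) has a required number of 28 and continues: "Anticipating a dropout/exclusion rate of around 10" per cent, "a total of 30 patients will need to be enrolled, with 15 patients allocated to each group". Section 2.1 has patients "randomly assigned in a 1:1 ratio" and says in general terms that all of them are assessed at T0, T1 and T2. Table 1 schedules WAB-R and SAQOL-39 g at those three times only. Section 2.6 (Data analysis) takes the change in WAB-R from before to after treatment as primary and fits a linear mixed model. The article names no analysis population.

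**The concern.** Stopping study treatment and leaving the trial are different events, and section 2.2.3 handles them as one. A patient who misses more than three consecutive days of treatment, but would willingly come for the T1 assessment, is withdrawn by rule. Several of the grounds can depend on the coil received or on how the patient is progressing: a reaction to stimulation, a worsening condition, the search for other stimulation.

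If such patients have no T1 score, the T1 comparison is between those who tolerated and completed treatment in each arm, not between the arms as randomised. With 15 patients per arm, two or three such losses matter. A T1 score that was never collected cannot be restored by any later choice of analysis set.

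**Working it through.** **Inputs from the article.** 15 patients per arm and a loss of about 10% (2.2.4); WAB-R at T0, T1 and T2 (Table 1); primary outcome the T0–T1 change (2.6); treatment over three weeks (2.4.3 and abstract).

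**Inputs that are assumptions.** The number k lost per arm, the shortfall D in AQ points, and the correlation between withdrawal and poor change. The documents give none of these.

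**Step 1. The plan's own loss figure.** 10% of 30 is 3 patients. If all three fall in one arm, that is 3/15 = 20% of it. After that loss, 30 × 0.90 = 27 remain, one fewer than the stated 28, so the design has no reserve against avoidable missing outcomes. The 28 itself depends on a correlation between time points that the article does not state. That is a separate matter, and nothing below turns on it.

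**Step 2. What a withdrawn patient contributes.** There is no WAB-R between T0 and T1. A patient withdrawn during treatment therefore has T0 only. The mixed model keeps that T0 value and in effect predicts the missing T1 from T0 and from the patients of the same arm who were seen. It corrects for whatever T0 predicts, but not for a reaction, a gap in treatment or a decline that occurred afterwards and is linked to the unseen score.

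**Step 3. Size in AQ points.** Let k of 15 patients be lost, with a true change D points below the rest of the arm beyond what T0 explains. The full-arm mean is the mean of the rest minus kD/15, so using the rest alone overstates the arm by kD/15. With the same D in both arms, the difference piTBS minus sham is shifted by (k₁ − k₀)D/15, where k₁ is lost from piTBS and k₀ from sham.

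| Lost from piTBS | Lost from sham | Shift, D = 5 | Shift, D = 10 |
|---|---|---|---|
| 3 | 0 | +1.00 | +2.00 |
| 2 | 0 | +0.67 | +1.33 |
| 2 | 1 | +0.33 | +0.67 |
| 2 | 2 | 0 | 0 |
| 1 | 2 | −0.33 | −0.67 |
| 0 | 3 | −1.00 | −2.00 |

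For example, 2 × 10/15 = 1.33 and 3 × 10/15 = 2.00. With D = 0 every entry is zero.

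**Step 4. Size in standard deviations of the change.** This is a simulation with no true treatment effect, in which withdrawal is correlated 0.3 to 0.5 with a poor change (assumed).

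- 2 lost from piTBS, 0 from sham: +0.08 to +0.13.
- 3 and 0: +0.11 to +0.18.
- 3 and 1: +0.07 to +0.11.
- 2 and 2: about 0.
- 1 and 2: −0.03 to −0.06.

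With no correlation the bias is zero in every case. If those who leave would have done better than the rest (correlation −0.3), the signs reverse: 2 and 0 gives −0.08.

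**Step 5. The two sections side by side.** Section 2.1 has every patient assessed at T0, T1 and T2. Section 2.2.3 ends participation for a defined subset and makes no provision for assessing them. The general statement does not settle what happens to a withdrawn patient, so the two must be reconciled.

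**The case against.** The strongest reply is that the article nowhere says withdrawn patients leave the analysis or go unassessed. Section 2.1 can be read as covering them, section 2.6 imposes no complete-case restriction, and a condensed article may leave the analysis set and post-withdrawal visits to the full protocol or the SAP. That stands as far as it goes: the absence of a named analysis population is not the point made here, and a reader should not infer that these patients are excluded from analysis. What remains is the stated rule, which is framed as leaving the trial.

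Other stronger readings are tempting and not supported:

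- **That the bias favours piTBS.** One might expect reactions mainly with the active coil, but the article gives no reaction rates by coil. The criteria are the same in both arms, and section 2.3 states that physicians, operators and evaluators are blinded. Worsening, or seeking other stimulation, could be commoner under sham, and losing those patients would work against piTBS.
- **That any discomfort or any new illness leads to withdrawal.** The first ground is governed by the word severe, and the third requires a judgement that continued participation is inappropriate.
- **That these reasons contradict missing-at-random.** A headache or a gap in treatment does not by itself imply a worse unseen AQ. The assumption is doubtful, not refuted.
- **That the 10% allowance is defined by section 2.2.3.** Section 2.2.4 makes no such reference. The link is plausible but inferred.

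**Conclusion.** The point holds as a weakness of design. Section 2.2.3 makes post-randomisation events, some of which may depend on treatment or progress, grounds for leaving the trial, and with no WAB-R between T0 and T1 the mixed model cannot recover the primary change of a patient withdrawn during treatment.

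Bias arises only if three things hold together: no T1 score is obtained after withdrawal, withdrawal is related to the unseen outcome, and the losses differ between arms in number or in kind. Under the assumptions shown, three losses in total could shift the difference by anything from −2.0 to +2.0 AQ points at D = 10. D is an illustration without a source in the documents, and neither sign nor size is established. No figure in the article is shown to be wrong by this point. It deserves attention because the remedy is inexpensive and must be in place before patients are withdrawn.

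**What to change.** Leave the criteria for stopping stimulation exactly as they are; when to stop is a clinical matter and is not judged here. Change only their consequence:

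1. State in section 2.2.3 that meeting a criterion ends study stimulation and not participation, and reconcile this with the statement in section 2.1 that all patients are assessed at T0, T1 and T2.
2. Invite every randomised patient who has not withdrawn consent to the WAB-R and SAQOL-39 g at T1 and T2, on the original schedule.
3. Include all randomised patients in their allocated arm in the primary analysis, with a compliers-only analysis as supportive.
4. Report withdrawals by arm and reason.

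The cost is a change of wording and a few T1 and T2 visits. The estimate will be somewhat diluted by partly treated patients. Patients who refuse assessment or withdraw consent will still be missing, so the change reduces the problem without removing it.

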#### Sample size

2.2.4

Based on the preliminary experimental results, the effect size [f(V)] for the piTBS group compared to the sham group in the primary outcomes is 0.25. With a significance level (α) of 0.05 and a power (1-β) of 0.95, considering a two-group design involving before and after treatment, and during follow-up assessments conducted at three time points, the anticipated sample size calculated using G*Power 3.1.9.7 for the repeated measures ANOVA model was 28. Anticipating a dropout/exclusion rate of around 10%, a total of 30 patients will need to be enrolled, with 15 patients allocated to each group.

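### The stated 95% power with 28 patients does not follow from the printed inputs: it needs an unstated between-visit correlation of about 0.68 or more, and it is wrong if the f(V) label is taken literally

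*Protocol article*

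**What the plan says.** Protocol article, section 2.2.4 (Sample size), prints what looks like a complete calculation:

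- Effect size: "the effect size [f(V)] for the piTBS group compared to the sham group in the primary outcomes is 0.25", attributed to preliminary results.
- Error rates: "With a significance level (α) of 0.05 and a power (1-β) of 0.95".
- Layout: "considering a two-group design involving before and after treatment, and during follow-up assessments conducted at three time points".
- Result: "the anticipated sample size calculated using G*Power 3.1.9.7 for the repeated measures ANOVA model was 28".
- Enrolment: "Anticipating a dropout/exclusion rate of around 10%, a total of 30 patients will need to be enrolled, with 15 patients allocated to each group".

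Section 2.1 adds that patients are "randomly assigned in a 1:1 ratio". Section 2.6 (Data analysis) plans a mixed model in which a significant group-by-time interaction leads to the post-hoc comparisons. Section 2.2.4 does not say whether the calculation was for that interaction, for the time effect or for the overall group difference. Neither section gives a correlation between visits or a sphericity value, and the article does not define f(V).

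**The concern.** In a repeated-measures power calculation based on an ordinary f, the correlation between visits decides the answer as much as f does. Without it, the printed inputs do not lead to a single sample size. The one effect-size label that is printed, f(V), points to a parameterisation in which no correlation is entered. On that reading 28 patients are far too few for 95% power. So either the label is wrong, or the sample size is wrong for that label.

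This bears on how the result will be read. The abstract describes the efficacy of the treatment as unclear. If the trial finds no difference, a reader who trusts the stated power will give it the weight of a test with a 5% type II error. Whether that weight is deserved cannot be told from what is printed.

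**Working it through.** **Inputs from the documents.** Effect size 0.25, so f² = 0.0625; alpha 0.05; target power 0.95; k = 2 groups; m = 3 time points; stated N = 28 (section 2.2.4). Allocation 1:1 (section 2.1), so N is taken as the smallest even number.

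**Assumptions, not in the documents.** Between-visit correlation ρ, varied from 0.3 to 0.8; sphericity (ε = 1); the test is the group-by-time interaction unless stated otherwise.

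**Step 1. Interaction test, 0.25 read as an ordinary f.** Power comes from the noncentral F distribution with λ = f²·N·m/(1−ρ), df1 = (k−1)(m−1) = 2 and df2 = (N−k)(m−1) = 2(N−2).

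At N = 28, df2 = 52 and the critical F is 3.175. The numerator of λ is 0.0625 × 28 × 3 = 5.25.

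| ρ | λ = 5.25/(1−ρ) | Power at N = 28 |
|---|---|---|
| 0.3 | 7.50 | 66% |
| 0.4 | 8.75 | 73% |
| 0.5 | 10.50 | 81% |
| 0.6 | 13.13 | 89% |
| 0.68 | 16.41 | 95.0% |
| 0.7 | 17.50 | 96% |
| 0.75 | 21.00 | 98% |
| 0.8 | 26.25 | above 99% |

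The plan's own figure is therefore reproduced under one condition. The smallest even N for 95% power is exactly 28 when ρ lies between about 0.68 and 0.70.

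**Step 2. Sample size for 95% power, by correlation.** The same formula, solved for N, gives 60 (ρ = 0.3), 52 (0.4), 44 (0.5), 36 (0.6), 28 (0.68 to 0.70), 24 (0.75) and 20 (0.8). At ρ = 0.5 the smallest even N is 28 for 80% power (achieved 0.812), 36 for 90% (0.906) and 44 for 95% (0.956).

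**Step 3. f(V) read literally, with no correlation input.** Two forms of λ span the main readings:

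- Univariate: λ = f²(N−k)(m−1). At N = 28, λ = 0.0625 × 26 × 2 = 3.25, with df 2 and 52; power is 0.328. For 95%, N = 128.
- Multivariate: λ = f²·N. At N = 28, λ = 0.0625 × 28 = 1.75, with df 2 and 25; power is 0.183. For 95%, N = 252.

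Small changes in how N enters λ move these to between 126 and 254 patients, and to between 17% and 35% power at 28. None comes near 28 patients for 95%.

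**Step 4. Other readings of the test.** For the overall between-group difference, λ = f²·N·m/(1+(m−1)ρ). At ρ = 0.5 and N = 28, λ = 5.25/2 = 2.625 with df 1 and 26; power is 0.345, and 95% needs 142. The within-patient time effect gives the same figures as step 1 in this layout.

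**Step 5. After the planned loss.** 30 × 0.9 = 27 patients. Interaction power at 27 is 0.795 at ρ = 0.5 and 0.955 at ρ = 0.7.

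**The case against.** The strongest reply is that a missing input makes the claim unverifiable, not false. That stands for the ordinary-f reading. The same language battery is given to the same patients before treatment, after three weeks of treatment and at the 4-week follow-up. Entry is open to any aphasia quotient below 93.8. With such a wide spread of severity, a correlation of 0.7 would be unremarkable, and it returns exactly 28. Above that value the stated 95% is conservative, and at 0.7 even the 27 patients left after dropout keep 95%.

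Three stronger conclusions are tempting, and the documents do not support them:

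- **That 0.80 was entered as the power instead of 0.95.** The match of 28 with the 80% answer at correlation 0.5 is suggestive, but a correlation near 0.7 explains 28 equally well.
- **That 44 patients are required, or that the type II risk is about four times the stated 5%.** Both hold only at correlation 0.5, which the article does not state.
- **That 142 patients are needed because the effect is described as one group compared with the other.** Section 2.6 builds its inference on the group-by-time interaction, so the overall group difference is not the natural test.

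It may also be said that an article can leave the correlation to the full protocol. That would excuse a bare omission. It does not excuse printing a headline power beside an effect-size label under which that power is wrong.

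**Conclusion.** The claim of 95% power with 28 patients does not follow from what section 2.2.4 prints. Under the printed f(V) label, taken literally, it is wrong: about 18–33% power at 28, and about 128–252 patients for 95%. It can be right only if 0.25 is an ordinary f, the test is the group-by-time interaction, sphericity holds and the between-visit correlation is about 0.68 or more. Over correlations from 0.3 to 0.8, power at 28 runs from 66% to above 99%, so the missing input settles whether the headline figure stands. The documents do not show which correlation applies. The finding is therefore that the stated power is unsupported and its label inconsistent with the sample size, not that the trial is shown to be underpowered.

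**What to change.** Rewrite the calculation in section 2.2.4, without adding patients:

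1. Name the test as the group-by-time interaction.
2. Correct the effect-size label. If 0.25 is an ordinary f, call it f. If it really is a variance-explained f(V), the stated power with 28 patients cannot stand.
3. State the between-visit correlation, with its source in the preliminary data, and the sphericity assumption.
4. Keep 95% only if those data support a correlation of about 0.68 or more. Otherwise restate the power at the supported value. If that were 0.5, for example, it would be about 81% with 28 evaluable patients and about 80% with 27.

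The cost is a sentence or two of text. The downside is that the stated power may become less favourable.

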### Randomization and blinding

2.3

The randomized sequence of numbers generated by SPSS software will be written in order and placed in opaque sealed envelopes. All eligible patients will be randomly assigned to one of the two treatment groups in the order of enrollment. Recruiters, study physicians, TMS operators, clinical staff, evaluators, data collectors and statistical analysts are blinded. These people will not know the group of patients.

### Interventions

2.4

The patients will be assigned under the 1:1 randomization formula, constituting two groups for the present study: 15 patients treated with piTBS +15 patients treated with sham stimulation. Furthermore, a designated speech rehabilitation therapist will assess the scale evaluations of all enrolled patients. A transcranial magnetic stimulator (Neurosoft, YD-MT500, Russia) with a figure-of-eight coil and a sham stimulation coil will be used. The coil position targeting the SMA is determined using the international 10–20 EEG system as a reference. The target stimulation site is set at 15% of the nasion-inion distance anterior to the Cz position, along the sagittal midline (40). The coil is positioned to form a 45°with the sagittal plane, in order to deliver stimulation to the left SMA.

#### Resting motor threshold

2.4.1

Patients will be instructed to attain a state of relaxation while maintaining their eyes open (41). The RMT is defined as the ability to induce Motor Evoked Potentials (MEPs) of no less than 50 millivolts in at least five out of 10 consecutive stimulations, measured at the right primary motor cortex.

#### Protocol

2.4.2

piTBS group: the piTBS will be adopted based on the standard iTBS protocol (a 2 s train of TBS repeated every 10 s at an intensity of 80% RMT and a total of 600 pulses) by increasing the number of pulses to 1,800. This will spend 9 min 42 s every session.Sham group: the sham group will receive treatment with the same target coordinates, parameters, dosage, but as sham coils.

#### Routine medical care

2.4.3

All patients will receive standard medication and rehabilitation therapy. Additionally, they will undergo speech and language therapy (SLT) for 1 h daily following treatment, five times a week, for 3 weeks. The training program is based on the Schuell’s stimulation approach, focusing primarily on language comprehension and expression.

### Outcomes

2.5

#### Behavioral assessments

2.5.1

##### Western Aphasia Battery Revised

2.5.1.1

The Western aphasia battery revised (WAB-R) is a standardized tool used to assess post-stroke aphasia. The aphasia quotient (AQ) is derived by adding the standardized scores from the WAB-R subtests of spontaneous speech, auditory comprehension, repetition, and naming. The AQ provides a composite index of language and communication skills, which less than 93.8 indicate aphasia (42).

##### The Stroke and Aphasia Quality of Life Scale

2.5.1.2

The Stroke and Aphasia Quality of Life Scale (SAQOL-39 g) is a self-report questionnaire specifically developed to evaluate the health-related quality of life in PSA patients (43, 44). The SAQOL-39 g consists of 3 dimensions: physical, communicative, and psychosocial. The physical dimension consists of 16 items, the communicative dimension consists of 7 items, and the psychosocial dimension consists of 16 items, for a total of 39 items. All items are rated on a 5-point scale, with higher scores indicating better quality of life. The SAQOL-39 g provides a brief, reliable measure of health-related quality of life that covers the sequelae of stroke.

##### The Edinburgh Handedness Inventory

2.5.1.3

The EHI is a straightforward survey utilized for evaluating hand preference and lateralization of hand proficiency. The EHI accurately distinguishes between left, right, and mixed hand preference (45). The questionnaire comprises 10 items that inquire about the dominant hand for common unimanual activities, including writing, throwing, and using scissors. Scores are determined by operational indicators, where a score of less than −40 designates left-handedness, a score between −40 and 40 indicates mixed-handedness, and a score exceeding 40 denotes right-handedness.

